## Abstract

**Background:**

Falls are the primary cause of fatal and nonfatal accidental injuries in older adults. The World Falls Prevention Guidelines recommend balance-challenging, functional exercise programs as a key strategy for falls prevention, but access, uptake, and adherence to these programs in community settings remain suboptimal. Keep-On-Keep-Up (KOKU), a digital, National Health Service–approved program, was codeveloped with older adults and therapists to provide progressive, evidence-based exercises and to raise awareness of falls prevention strategies.

**Objective:**

This trial aims to investigate the effectiveness and cost-effectiveness of the KOKU digital strength and balance program for improving balance, enhancing physical function, and reducing falls risk among community-dwelling older adults.

**Methods:**

This is a 2-arm, parallel-group randomized controlled trial. A total of 196 community-dwelling older adults 60 years and older will be randomized to either the intervention group, comprising a digital strength and balance program (KOKU) alongside standard care (strength and balance exercise advice and a falls prevention leaflet), or to a control group, receiving standard care only. Participants receiving the intervention will be asked to exercise 3 times per week following the tailored and progressive program. Randomization will take place after recruitment and baseline data collection. The trial’s primary outcome measure is balance function (Berg Balance Score) at 12 weeks post randomization. Secondary trial outcomes include lower limb strength, health care utilization and health-related quality of life, self-reported concerns about falling, self-reported physical activity, falls risk, pain, mood, fatigue, self-reported falls, and acceptability and usability of the KOKU program. Intention-to-treat analysis and a cost-effectiveness analysis will be employed for trial data analysis. Qualitative interviews and focus groups will be undertaken with around 10 care providers and 13 participants to further understand views of the intervention and trial processes.

**Results:**

This study began recruitment in July 2024 and concluded in March 2025, recruiting a total of 202 participants (102 intervention group and 100 control group). Following protocol publication, data compilation and analysis will be conducted, with results anticipated to be published in 2027.

**Conclusions:**

This trial will provide important evidence on whether a digital strength and balance program can improve balance and related outcomes in older adults compared with usual care.

## Introduction

With population aging, supporting older adults to live longer, healthier, independent lives is a major societal challenge [1]. Falls are a common problem for older adults, with risk increasing exponentially with age, leading to growing health and social care costs [2,3]. These include ambulance callouts, fractures, hospital admissions, premature admission to care homes, and increased dependency. The Office for Health Improvement and Disparities estimates that in England, the total annual cost of falls-related fragility fractures was £4.4 billion (~US $6 billion) [4]. Systematic reviews of randomized controlled trial (RCT) evidence conclude that there is good evidence that strength and balance exercises are the most effective approach to improve function and reduce falls [5,6]. Effectiveness increases if the programs are challenging, of sufficient dose, progressive, and maintained [7].

In the United Kingdom, strength and balance training programs are usually delivered in community centers by qualified professionals. These programs can be effective but may be inaccessible to those who are homebound, without transport, and unavailable in some locations [8].

A growing evidence base suggests that digital interventions may be a feasible tool for the delivery of falls prevention and exercise programs among older adults [9-11]. Moreover, digital formats can incorporate health behavior change techniques such as goal setting, progress tracking, and feedback on individual progress and can be more user-friendly and appealing, which may improve engagement and adherence [12]. In comparison with face-to-face alternatives, digital platforms are relatively inexpensive, scalable, and can be safely used in the user’s own home at their convenience [12,13].

Keep-On-Keep-Up (KOKU) is a UK National Health Service (NHS)-approved digital health intervention for falls prevention [14]. KOKU can be used independently by older adults to instruct them how to undertake progressive strength and balance exercises based on the Otago Exercise Program and the Falls Management Exercise Program (FaME) [15,16]. KOKU also has 6 health literacy games to raise awareness of home hazards and ways to improve bone health, brain health, nutrition, and hydration. KOKU’s development was guided by the Healthtech Innovation Cycle [17], the EAST Behavioral Insights Framework [18], and the Medical Research Council guidance for designing and evaluating complex interventions [19]. KOKU has been iteratively co-developed with therapists and older adults, informed by international guidelines for falls prevention [7], a meta-analysis of exercises for falls prevention [6], health behavior change techniques [20], and consensus studies with outcome and reporting recommendations for falls prevention strategies [21].

This is one of the first digital evidence-informed strength and balance programs with both progressive exercises and gamified education for older people that acts as an intervention to prevent falls and functional decline. Feedback from users and stakeholders in usability and acceptability studies in the United Kingdom [22] and the United States [9] has been positive.

In this paper, we describe an RCT to evaluate the effectiveness and cost-effectiveness of a digital exercise program, KOKU, for improving balance and function and reducing falls risk in community-dwelling older adults aged 60 years and above.

## Methods

### Public and Community Involvement and Engagement

Patient and public involvement was used to inform the design of the first iteration of the KOKU program and has continued to be important for ongoing development and to inform the design of the trial. Patient and public involvement feedback has led to the development of KOKU in both iOS and Android formats to be more digitally inclusive and informed the study methods such as how to recruit participants through care providers. The study is supported by the NIHR Applied Research Collaboration Greater Manchester (ARC-GM), which has a public and community involvement and engagement lead who has convened 2 meetings during the preparation of the study methods to ensure that a diverse group of older adults’ views were incorporated into the research processes. During the design phase of this study, the research team visited community organizations supporting social care (ie, not health service providers) to explain the study and gain an insight into the organization’s daily activities and operations to inform study processes.

### Trial Design

The 2-arm parallel-group RCT will compare the effectiveness of a digital strength and balance program (KOKU) plus standard care (strength and balance exercise advice and a falls prevention leaflet) against standard care alone. The study will test the effectiveness and cost-effectiveness of the KOKU program, and the primary outcome measure will be balance, as measured by the Berg Balance Scale [23].

This study is funded by the NHS England CareTech Program, which has a remit to identify care technology solutions and provide support to gain robust evidence that could have potential for wider rollout within the care sector. The trial opened to recruitment in July 2024 and closed in March 2025, with findings expected to be published in 2027. This protocol paper follows the SPIRIT (Standard Protocol Items: Recommendations for Interventional Trials) guidelines [24] (Checklist 1) and the TIDieR (Template for Intervention Description and Replication) checklist for the description of the intervention [25] (Checklist 2).

### Participants

Participants will be recruited from a variety of organizations and social care providers based in community settings in Greater Manchester and Lancashire areas in the Northwest of England. These include adult social care teams, housing providers, and charity organizations that support older adults to remain as independent as possible in their own homes. The community organization providers will be recruited via the Greater Manchester local authorities’ adult social care managers, who will then act as gatekeepers to recruit older adults. All eligible research participants will receive a participant information sheet and will be asked to complete an informed consent form by the research team, attesting to their voluntary participation in the study.

Participants will include community-dwelling older adults aged 60 years and over, referred via community care providers in Greater Manchester and Lancashire, and eligible to take part in the study if they have the following characteristics:

are willing and able to give informed consentspeak Englishare able to see and safely use the tablet-based KOKU programcan read instructions with or without glasses, as assessed by the trained research staffare able to mobilize indoors without the help of another person, with or without a walking aid (self-reported)

The exclusion criteria for the older adult participants are as follows:

those who are currently using digital technologies to exercisecurrently taking part in an exercise program or undertaking physiotherapythose who are unable to comprehend the study proceduresthose who have medical contraindications to exercise due to unstable health or severe conditions (eg, acute illness, severe congestive cardiac failure, uncontrolled hypertension, recent fracture or surgery; myocardial infarction or stroke in past 6 mo; severe cognitive impairment; orthopedic surgery in last 6 mo or on a waiting list to have orthopedic surgery; wheelchair users; severe auditory or visual impairment; or other uncontrolled medical conditions likely to compromise the ability to exercise)

We also aim to recruit care provider staff (n=10) and a purposive sample of the participating older adults (n=13) to participate in a qualitative interview or focus group at the end of the intervention period to provide insights and feedback on the usability of the KOKU program and the trial processes.

Recruitment, randomization, data analysis, and interpretation will be undertaken by the Applied Research Collaboration-Greater Manchester (led by PB), independent from KOKU Health.

### Randomization and Blinding

Randomization will be performed using Research Electronic Data Capture (REDCap V 14.0.31 [26]) randomization module to allocate older adult participants in a 1:1 ratio to either the intervention or control group. Random permuted blocks of various sizes will be used to produce similar group sizes and preserve allocation concealment. The allocation sequence will be computer-generated and uploaded into the REDCap system by a researcher who is not involved in enrolling or assigning participants to groups.

Responsibility for enrolling participants into the trial lies with the principal investigator and staff at the sites. Allocation concealment will be ensured, as the system will not release the allocation until the participant has been randomized by a researcher not involved in recruitment, after baseline assessments have been taken. Given the nature of the trial, researchers completing data collection and participants will not be blinded. The researcher undertaking data analyses will be blinded to the intervention and control groups to minimize bias.

### Intervention

Participants allocated to the intervention group will receive an iPad for the intervention period and will be recommended to train with KOKU for 20 to 30 minutes, 3 times per week for 12 weeks. The researcher will explain and also provide written instructions on how to use the iPad and the KOKU program, including how to switch on and charge the device. Upon first opening the KOKU program, participants are asked to complete a short onboarding questionnaire (eg, age and gender) and a walkthrough featuring written, audio, and animation instructions. The researchers will give their contact details so additional digital literacy support can be provided in person or via phone calls, if required.

The digital program includes 26 strength and balance exercises that progress from seated to standing and walking exercises. As participants complete the program, the exercises progress according to responses to questions such as “Do you feel out of breath?“ or “Could you perform the exercises easily?” Each exercise has safety information and an animated coach who demonstrates correct movements with audio and written information. The exercises include heel raises, sit-to-stands, side leg raises (abductors), side, front, and back lunges, heel-to-toe walking, sideways walking, and walking backward. If participants forget to complete their weekly exercises, they are sent an app notification after 1 week to remind them to continue.

After each exercise, participants can see how many training sessions have been completed on a progress screen embedded within the KOKU program and how many sessions remain before the 12-week intervention is completed.

The KOKU program is informed by behavior change theory and techniques such as gamification to improve access and uptake of strength and balance exercises. In addition to the exercises, there are 6 complementary health literacy games to help users learn about how to promote bone health, nutrition, hydration, and safety in the home. The bone health game, for example, asks participants to choose items from a fridge that are known to deplete or enhance calcium, vitamin D, and associated nutrients or minerals. The animated character’s X-ray bones grow or shrink, and a bone barometer increases or decreases. Evidence-based messages in lay language are presented after each selection to explain why a choice of food or drink is beneficial or not for improving bone health. The embedded health literacy games were developed with international experts and are popular with users due to the gamified elements that increase engagement and enjoyment. A user instruction video provides a short demonstration of how to download and use KOKU [27].

Participants in the intervention group will also receive home exercise leaflets based on FaME [15] and Otago Exercise Program [16], and falls prevention advice alongside the KOKU digital program.

Participants in the control group will receive the same leaflets without KOKU and will be asked to undertake the exercises listed in the leaflet 3 times a week in their leisure time.

### Outcomes

At baseline, a bespoke questionnaire will capture past medical history (including fractures), medication, comorbidities, self-reported level of vision, and demographic data (age, gender, ethnicity, and socioeconomic status). Outcome data will be collected by trained researchers from all participants at baseline, 6 weeks, and at the end of the 12-week period (Table 1).

**Table 1. T1:** KOKU^a^ trial schedule of enrollment, interventions, and assessments.

Timepoint	Prescreening	Enrolment/allocation	Study period postallocation			
			Baseline	Week 6	Week 12	Week 24
Recruitment—research team						
Identify potential care providers for study	✓					
Familiarize care providers with research project	✓					
Recruitment—care providers						
Identify potential study participants	✓					
Patient enrollment						
Eligibility screen	✓	✓				
Informed consent		✓				
Training to use KOKU		✓				
Interview/focus group					✓	
Care provider staff enrollment						
Eligibility screen		✓				
Informed consent		✓				
Training to use KOKU		✓				
Interview/focus group					✓	
Allocation—Interventions						
KOKU			✓	✓	✓	
OEP^b^ leaflet and falls prevention leaflet			✓	✓	✓	
Assessments						
BBS^c^			✓	✓	✓	
5StS^d^			✓	✓	✓	
Health questionnaires^e^				✓	✓	
Adverse events			✓	✓	✓	
Usability/acceptability questionnaires^f^					✓	
Daily falls calendar follow-up			✓	✓	✓	✓

a KOKU: Keep-On-Keep-Up.

b OEP: Otago Exercise Programme.

c BBS: Berg Balance Scale.

d 5StS: Five Times Sit-to-Stand chair test.

e Health questionnaires include 5-item Geriatric Depression Scale, Physical Activity Scale for the Elderly, Short Falls Efficacy Scale-International, Assessment of Falls Risk tool, and EQ-5D-5L.

f Usability/acceptability questionnaires include the System Usability Scale, the Short Version of the User Experience Questionnaire, and the theoretical framework for acceptability.

The primary outcome measure is balance function, as measured by the validated Berg Balance Scale (BBS) [23]. The test involves 14 assessments of static and dynamic balance and is useful in predicting the risk of falls and indicating an individual’s ability to mobilize and carry out activities of daily living.

Secondary outcomes measured at 6 and 12 weeks will be measured by the following assessments:

The Five Times Sit-to-Stand (5-STS) chair test [28] will be completed to assess lower limb strength. For this test, the participant is asked to stand up and sit down as quickly as possible 5 times from a standard-height chair (43.2 cm) with their arms folded. The researcher records the time taken to complete the test.Health-related quality of life will be measured using the EQ-5D-5L [29], which considers 5 dimensions: mobility, self-care, usual activities, pain or discomfort, and anxiety. Each dimension is rated as one of the following 5 options: no problems, slight problems, moderate problems, severe problems, and extreme problems.Mood will be assessed using the 5-item Geriatric Depression Scale. This screening tool for depression in older adults is validated to be as effective as the 15-item Geriatric Depression Scale in a wide range of settings [30].The level of physical activity will be measured using the Physical Activity Scale for the Elderly questionnaire [31]. This is a validated and easy-to-administer questionnaire designed to assess physical activity in those 65 years and older.Concerns about falling will be measured using the Short Falls Efficacy Scale—International [32]. The Short Falls Efficacy Scale—International is a validated and reliable 7-item tool that measures concerns about falling in relation to a range of everyday activities and is available in a number of languages [32,33].The risk of falling will be assessed using the assessment of falls risk tool. This validated measure [34] has 5 items, which include a history of any fall in the previous year, 4 or more prescribed medications, diagnosis of stroke or Parkinson disease, reported problems with balance, and inability to rise from a chair without using arms. A visual analog score for pain and fatigue will be included, as these are all strong indicators of risk of falling.Secondary outcomes will also consider the usability and acceptability of KOKU. At the 12-week assessment, participants in the intervention group will complete questionnaires focusing on usability, acceptability, and motivation to use KOKU. The System Usability Scale will assess the usability of KOKU from the users’ perspective [35]. The theoretical framework for acceptability will assess perceived acceptability of the KOKU system [36]. The short version of the User Experience Questionnaire will assess the usability of the KOKU system [37].Falls will be assessed using daily self-report fall calendars for 24 weeks, with follow-up phone calls from a researcher to find out more details of any falls reported and any use of health care resources. This will include details on how the fall occurred, if a visit to a general practitioner (GP), hospital, or emergency department was required, and if the fall resulted in a fracture, swelling, or other self-reported injury. Fall severity will be coded as no injury, moderate injury, or serious injury based on consultation between 2 authors (CF, ES), including a registered nurse and without discussion of group allocation. Falls and all injuries will be recorded during the 6-month period, with falls defined as “an unexpected event in which participants come to rest on the ground, floor, or other lower level” [21].Health care resource use: Resource use data will be collected during follow-up to measure health service utilization related to falls. This includes ambulance attendances, accident and emergency visits, general practitioner consultations, and hospital admissions (public or private). This will be analyzed descriptively as a secondary outcome and will inform the cost-effectiveness analysis.

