### Sample Size

Parameter estimates are based on a previous study of a digital intervention for adults in community settings with BBS as the primary outcome measure at 12 weeks [12]. Based on data from this previous study, we estimate the SD to be 14. Correlation between baseline and follow-up was 0.81 in the previous trial, but we will use a conservative value of 0.7. To achieve 90% power at a 5% significance level, with inflation for 13% attrition, we estimate that a sample size of 196 (98 per arm) is required to demonstrate the minimal clinically important change needed to reduce falls risk and improve functional balance of a difference in means of 5 points on the BBS at 12 weeks [39]. A minimal clinically important change of 5 points in the BBS was chosen according to baseline BBS scores of 35 to 44 observed in a previous study of older adults in the same region where the trial will be conducted [12].

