### Statistical Analysis

All statistical analyses will be performed using Stata (StataCorp) or SPSS (version 28, IBM Corp; 2021).

Baseline demographic and clinical characteristics will be summarized by trial arm using means and SD, or median and interquartile ranges for continuous variables, as appropriate, and frequencies with percentages for categorical variables.

The primary analysis will be conducted following the intention-to-treat (ITT) principle, including all participants providing evaluable outcome data irrespective of their engagement with the KOKU program or control intervention.

BBS will be analyzed using a mixed model for repeated measures (MMRM). The model will include the fixed effects of trial arm (ie, KOKU and control), time point (ie, 6 and 12 wk), and the fixed covariate of baseline scores, as well as the interactions of all fixed terms by time point, ensuring the effects are permitted to vary for each of the 2 time points. An unstructured covariance matrix will be used, and the model will be fitted using restricted maximum likelihood (RML) estimation. The primary comparison of interest is between group differences at 12 weeks. Results will be presented as regression coefficients with 95% CIs. Continuous secondary outcomes will be analyzed using a similar framework to the primary outcome.

The rate of falls will be analyzed using a parametric model for count data (eg, Poisson or negative binomial), adjusting for baseline values. The appropriate model will be chosen depending on the distribution of this variable. The incident rate ratio will be presented with a 95% CI.

All the models will be adjusted for baseline values. Thus, to minimize data loss, simple mean imputation (across the randomized groups) of the corresponding outcome data will be used. MMRM models are likelihood-based and therefore consistent with the missing-at-random assumption. Sensitivity analyses to assess the robustness of the MAR assumption will be performed for the primary outcome.

Quantitative data will be managed using REDCap [26], a secure, web-based software platform designed to support data capture for research studies, providing (1) an intuitive interface for validated data capture; (2) audit trails for tracking data manipulation and export procedures; (3) automated export procedures for seamless data downloads to common statistical packages; and (4) procedures for data integration and interoperability with external sources.

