### Economic Analysis

The primary objective of the economic analysis is to assess the incremental cost-effectiveness of the KOKU program compared with usual care. A cost-effectiveness analysis (CEA) will be conducted alongside the trial from the NHS perspective, excluding patient-incurred costs. The base-case CEA will adopt a 12-week time horizon, consistent with the trial follow-up period.

Health care resource–use data collected during the telephone follow-ups of participants who report a fall will be combined with relevant unit cost data for the financial year 2023 to 2024 to calculate the total costs incurred over the study period. Unit costs will be obtained from available UK health care reference sources. For primary care, the latest Personal Social Services Research Unit reference costs will be used, while for secondary care, costs will be sourced from the latest national reference cost schedule.

Quality-adjusted life years (QALYs) will be calculated based on EQ-5D-5L utility values using the area-under-the-curve method, assuming linear extrapolation of utility between time points. EQ-5D-5L will be scored using the appropriate tariff as recommended by the National Institute for Health and Care Excellence at the time of data collection. Multiple imputation techniques will be used to handle missing data in the main analysis, with the number of imputations determined by the extent of missing data. Regression analysis will estimate incremental costs and QALYs between the intervention and control groups, adjusting for baseline covariates including sex, age, ethnicity, marital status, socioeconomic status, and baseline utility score. Model selection (such as ordinary least squares/general linear models) will be based on goodness-of-fit statistics and diagnostic tests for model specification. Incremental net-monetary benefit will be calculated using a willingness-to-pay threshold of £20,000 (~$26,900) per QALY. Cost-effectiveness acceptability curves will be produced to show the probability of cost-effectiveness across a range of thresholds.

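### The primary Berg Balance Scale (BBS) model is valid and adequately powered, but prespecifying age and gender as covariates would be a small, nearly free improvement

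*Protocol article*

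**What the plan says.** Four places in the protocol article bear on this.

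- **Outcomes:** "At baseline, a bespoke questionnaire will capture past medical history (including fractures), medication, comorbidities, self-reported level of vision, and demographic data". The demographics listed there include age and gender. Table 1 also ticks the Five Times Sit-to-Stand test (5-STS) at baseline.
- **Randomization and Blinding:** "Random permuted blocks of various sizes will be used to produce similar group sizes and preserve allocation concealment". Allocation is 1:1, and no stratification factor is named.
- **Statistical Analysis:** the BBS model has arm, time point "and the fixed covariate of baseline scores, as well as the interactions of all fixed terms by time point". It uses an unstructured covariance and relies on missing at random (MAR). Sensitivity analyses to that assumption are promised for the primary outcome.
- **Economic Analysis:** the cost and QALY regressions are described as "adjusting for baseline covariates including sex, age, ethnicity, marital status, socioeconomic status, and baseline utility score".

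**The concern.** Age and gender may predict 12-week BBS beyond what baseline BBS already explains. If they do, putting them in the model narrows the confidence interval for the primary comparison. It also removes the part of the estimate that comes from chance imbalance in those variables, which the randomization as described does not control.

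The second issue is missing data. A likelihood-based model relies on MAR given the variables it contains. If the relation between age and dropout differs by arm, a model without age can be slightly off.

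At stake is a modest amount of precision and some robustness. The validity of the primary analysis is not in question.

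**Working it through.** **Inputs from Sample Size.**

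- Spread of the outcome: "we estimate the SD to be 14".
- Error rates and attrition: "To achieve 90% power at a 5% significance level, with inflation for 13% attrition". A two-sided test is assumed, since sidedness is not stated.
- Target effect: "a difference in means of 5 points on the BBS at 12 weeks".
- Strength of the baseline adjustment: "Correlation between baseline and follow-up was 0.81 in the previous trial, but we will use a conservative value of 0.7".

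**Step 1: reproduce the plan's figure with baseline BBS as the only covariate.**

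- Residual SD = 14 × √(1 − 0.7²) = 9.998.
- n per arm = 2 × [9.998 × (1.960 + 1.282) / 5]² = 84.03, rounded up to 85.
- With attrition: 85 / 0.87 = 97.7, so 98 per arm and 196 in total. This matches the article.
- SE = 9.998 × √(2/85) = 1.534. Power = Φ(5/1.534 − 1.96) = 90.3% (90.0% with the noncentral t).
- Without baseline adjustment, 165 per arm would be needed. Baseline BBS already does most of the work.

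**Step 2: add covariates.** Let p be the partial R² of the added covariates given baseline BBS. The article does not give it, so the range is an assumption. Residual SD = 14 × √[(1 − r²)(1 − p)], with 85 evaluable per arm.

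| p (assumed) | Residual SD, r = 0.7 | SE, r = 0.7 | Power, r = 0.7 | Total N for 90%, r = 0.7 | Power, r = 0.81 |
|---|---|---|---|---|---|
| 0 | 9.998 | 1.534 | 90.3% | 196 | 97.8% |
| 0.02 | 9.898 | 1.518 | 90.9% | 192 | 98.0% |
| 0.05 | 9.745 | 1.495 | 91.7% | 184 | 98.3% |
| 0.10 | 9.485 | 1.455 | 93.0% | 176 | 98.7% |

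The SE falls by 1.0%, 2.5% and 5.1%. Power rises by 0.6 to 2.7 points at r = 0.7 and by 0.2 to 0.9 points at r = 0.81.

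These figures leave out the cost of estimating two more coefficients. With 170 evaluable participants that raises the variance by a factor of about (1 + 3/164) / (1 + 1/166) = 1.012, or about 0.6% on the SE. At p = 0.02 the net reduction in SE is therefore nearer 0.4%, since √(0.98 × 1.012) = 0.996.

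**Step 3: dropout.** Assume KOKU participants drop out at 22% in the older half and 4% in the younger half, with 13% in the control arm unrelated to age. Assume also that age is uncorrelated with baseline BBS and has a partial correlation of −0.15 to −0.35 with 12-week BBS.

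- Mean standardized age of KOKU completers = 0.798 × (0.78 − 0.96) / (0.78 + 0.96) = −0.083.
- Bias without age, ignoring week 6 = 0.083 × 0.15 × 9.998 = 0.12 points, up to 0.083 × 0.35 × 9.998 = 0.29 points. That is 0.08 to 0.19 of one SE, in favor of KOKU.
- The planned model also uses week-6 BBS. Suppose all dropout follows week 6, age relates equally to BBS at both visits, and the residual correlation c between visits is 0.5 to 0.7. The bias is then multiplied by about (1 − c): 0.12 × 0.3 = 0.04 to 0.29 × 0.5 = 0.14 points. Dropout before week 6 gets no such protection.

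A separate simulation used 98 per arm, 4,000 replicates and p for age of 0.02 to 0.10. It modeled dropout as logistic in age and ignored week 6.

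| Dropout pattern (assumed) | Bias without age | Bias with age |
|---|---|---|
| Same age relation in both arms | within 0.03 | within 0.03 |
| KOKU arm only, moderate (log odds 0.7 per SD of age) | 0.14 to 0.33 | within 0.04 |
| KOKU arm only, strong (log odds 1.2 per SD of age) | 0.28 to 0.63 | within 0.01 |

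**The case against.** The strongest reply is that nothing here is wrong. A repeated-measures model adjusted for the baseline outcome, with effects allowed to vary by visit, is a sound primary analysis of a randomized trial. The sample size was built on that adjustment, and no named stratification factor is left out of the model. Chance imbalance is already reflected in the confidence interval. All of this stands.

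It is also fair that the partial R² is assumed, and that 202 participants were enrolled against 196 planned. If the earlier trial's correlation of 0.81 holds, there is little power left to gain. A fuller covariate list might appear in an analysis plan that is not shown, and absence of stratification is read from silence in a condensed article. These points limit the size of the recommendation. They do not remove it, because the article does state the terms of the model.

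Three stronger readings are tempting, and the article supports none of them.

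- A reader might infer that precision is being thrown away. The main prognostic variable is in the model, and the remaining gain is a few percent at most over the range considered.
- A reader might infer that more dropout among older KOKU participants is enough to bias the result. It is not: when age drives dropout equally in both arms, the bias is negligible. Arm-specific dropout is conceivable, since only one arm has to use an iPad program, but the article gives no evidence of it.
- A reader might see an inconsistency with the economic regression. That regression concerns costs and QALYs, and nothing requires the two analyses to share covariates. It shows only that the team intends to use age and sex elsewhere.

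A last objection is that changing the model after recruitment has closed, with unblinded data collectors, invites suspicion. That is a reason to record the change before unblinding and to keep the present model visible.

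**Conclusion.** The point holds as a minor efficiency and robustness recommendation. The planned model is valid and delivers its stated power.

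For an assumed partial R² of 0.02 to 0.10, the SE falls about 1% to 5%, less about 0.6% for the extra coefficients. Power rises about 0.6 to 2.7 points at r = 0.7 and 0.2 to 0.9 points at r = 0.81. Age and gender alone cannot explain more than they would together with 5-STS, so the upper end should not be counted on.

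Protection against dropout bias is worth up to about 0.1 to 0.3 BBS points under moderate assumptions, against a target difference of 5. It is worth more only under strongly arm-specific dropout, and less once week-6 BBS is available. It needs two conditions that the article does not show: dropout that depends on age differently by arm, and age predicting week-12 BBS beyond baseline and week-6 BBS.

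**What to change.** Before unblinding, add age (continuous) and gender as prespecified fixed covariates in the primary BBS model, each by time point, and record the date of that decision. Keep the model with baseline BBS only as a sensitivity analysis.

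Baseline 5-STS is optional. The test is recorded as a completion time, so using it as a covariate needs a stated rule for participants who cannot complete it.

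The cost is a sentence in the analysis plan and two extra coefficients per visit, out of about 170 evaluable participants. No new data are needed. The Results section places analysis after publication of the protocol, so on the article's own timetable the change can still be prespecified.
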